### Statistical analysis

The full analysis set (FAS) population will include all randomized participants who receive at least 20 mL trial medication and collect outcome data after treatment. It will be used to describe the analysis set which is as complete as possible and as close as possible to the intention-to-treat ideal of including all randomized participants. Per-protocol (PP) population will include all randomized patients who strictly follow the protocol. The safety set (SS) population will include all randomized participants who receive at least 20 mL trial medication and have safety evaluation data. Missing efficacy data will be imputed using the last observation carried forward method. Efficacy and safety analysis will be performed based on the FAS and PP population and SS population.

Statistical analysis will be performed using SAS 9.4 according to the statistical analysis plan. The primary outcome of cough resolution rate will be analyzed using the chi-squared or Fisher’s exact tests. Furthermore, logistic regression will be conducted to provide a risk ratio. For secondary outcomes, *t* test and nonparametric tests will be used for quantitative data, and chi-squared or Fisher’s exact tests will be used for qualitative data. A one-sided *P*-value of 0.025 or less will be considered statistically significant.

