### Withdrawal and termination criteria

Researchers can withdraw participants for the following reasons: (1) patients’ body temperature rises to 39 °C or more suggesting that other treatments may be needed (2); patients’ symptoms significantly worsen after three treatment days, in this case, trial drugs may need to be stopped and other treatments may need to be provided (3); patients develop serious adverse events (SAEs) or allergic reaction (4); patients accompany with severe comorbidities or complications (5); patients use forbidden medications; and (6) blindness is broken or need to be uncovered urgently for certain reasons. Participants themselves can voluntarily withdraw from the study at any time for any reason. In this case, researchers will make efforts to know and record their withdrawal reasons as much as possible, such as poor efficacy, intolerable to certain adverse reactions, economic factors, lost to follow-up without explanation, or other reasons for dropout.

National Pharmaceutical Supervisory and Administrative Department can terminate the whole trial for any reason. The primary investigators may terminate or suspend the study due to SAEs, poor efficacy, or significant deviation from the protocol during the study. The sponsors can also terminate the study because of SAEs or poor efficacy.

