### Interventions

All patients will be randomly allocated to either the Tanreqing group or the placebo group. Patients in either group will receive Tanreqing oral liquid or placebo liquid, 20 mL three times daily for seven consecutive days. Figure 2 provides the details of the study procedures.

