### Adverse event reporting

An adverse event (AE) will be any unexpected or undesirable experience or condition throughout the treatment period, including clinical symptoms or signs irrelevant to AB, and abnormal laboratory findings. All AEs will be recorded in detail including specific presentation, occurrence date, degree, duration, the process, treatment measures, clinical outcome and prognosis. The causal relationship between an AE and trial drug will be timely judged according to the general guidelines for clinical research of new drugs of traditional Chinese medicine (November 2015) issued by China State Food and Drug Administration. A SAE will be defined as any adverse medical event that occurred at any dose at any time throughout the whole trial. SAEs may (1) result in death, (2) be life-threatening, (3) result in persistent or significant disability or incapacity, (4) require inpatients hospitalization or extend the length of hospital stay, or (5) be other important medical events in which the abovementioned conditions may occur without treatment. Any SAE must be reported to the Biomedical Ethics Committee of West China Hospital of Sichuan University, the sponsor, and China’s State Food and Drug Administration within 24 h.

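### The safety set starts at one complete 20 mL dose, so a patient who reacts and stops partway through the first dose is in no analysis set

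*Protocol article*

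**What the plan says.** The Statistical analysis section of the protocol article defines three populations.

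- **Safety set:** "The safety set (SS) population will include all randomized participants who receive at least 20 mL trial medication and have safety evaluation data".
- **Full analysis set:** "all randomized participants who receive at least 20 mL trial medication and collect outcome data after treatment".
- **Per-protocol set:** "Per-protocol (PP) population will include all randomized patients who strictly follow the protocol".

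The section bases the efficacy and safety analyses on these three sets and names no other.

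Under Interventions, both arms take "20 mL three times daily for seven consecutive days". The 20 mL in the set definitions is therefore exactly one scheduled dose.

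The section on adverse event reporting has no minimum volume. It states: "An adverse event (AE) will be any unexpected or undesirable experience or condition throughout the treatment period". A serious event is "any adverse medical event that occurred at any dose at any time throughout the whole trial". Withdrawal and termination criteria lists among the reasons for withdrawal that "patients develop serious adverse events (SAEs) or allergic reaction", so the protocol foresees stopping after a reaction.

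**The concern.** A safety population should contain everyone who was exposed. Here entry depends on having taken a full first dose, and whether a patient finishes that dose can itself depend on how the drug is tolerated. A patient who drinks part of the first dose, reacts and stops is removed from the safety analysis because of the reaction the analysis is meant to count.

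Safety is a stated aim and adverse events are a listed outcome. Under Coordination and conduct of the trial there is no data monitoring committee and no interim safety analysis, so the final safety-set comparison is the main planned look at safety by arm. Under Sample size calculation, the Tanreqing arm also supplies a planned half of a 300-subject regulatory exposure requirement. Any immediate intolerance of the oral liquid should be visible in its adverse event rates.

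**Working it through.** This is mainly a check of definitions. The plan states no figure to reproduce.

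**Step 1: the threshold in doses.** Inputs from Interventions: 20 mL per dose, 3 doses a day, 7 days.

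- Full course: 20 × 3 × 7 = 420 mL in 21 doses.
- Threshold: 20 / 420 = 4.8% of the course, or 1 dose of 21.

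**Step 2: follow one patient through the definitions.** Suppose a patient takes more than 0 but less than 20 mL, has a reaction and stops.

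| Rule | Result |
|---|---|
| Adverse event recording | Applies; no minimum volume |
| Serious event reporting within 24 h | Applies if the event is serious; no minimum volume |
| Full analysis set | Out: less than 20 mL |
| Per-protocol set | Out: did not follow the schedule |
| Safety set | Out: less than 20 mL |

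No defined set holds this patient. A patient who finishes the 20 mL and reacts afterwards meets the volume rule, so the gap concerns only those who stop before completing one dose.

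**Step 3: how many patients.** The documents give no rate. As an assumption, let a proportion r stop before completing 20 mL. The expected number on Tanreqing is 180r, and the chance of at least one is 1 − (1 − r)^180.

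| Assumed r | Expected of 180 | Chance of at least one |
|---|---|---|
| 0 | 0 | 0 |
| 0.1% | 0.18 | 16% |
| 0.5% | 0.9 | 59% |
| 1% | 1.8 | 84% |
| 2% | 3.6 | 97% |

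**Step 4: what the safety table would show.** Let k be the number of Tanreqing patients who react before completing the first dose and stop, and suppose everyone else enters the set. All exposed patients give k/180; the stated rule gives 0/(180 − k) for these reactions. Upper limits are those of the exact (Clopper-Pearson) two-sided 95% interval.

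| Assumed k | All exposed | Upper limit | Under the stated rule | Upper limit |
|---|---|---|---|---|
| 0 | 0/180 = 0% | 2.03% | 0/180 = 0% | 2.03% |
| 1 | 1/180 = 0.6% | 3.06% | 0/179 = 0% | 2.04% |
| 2 | 2/180 = 1.1% | 3.96% | 0/178 = 0% | 2.05% |

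The values of k are illustrations. With k = 0 the rule changes nothing.

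**The case against.** Four points can be made for the plan.

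1. **At least 20 mL may simply mean at least one dose**, a common exposure criterion, and most first-dose reactions would follow a completed dose. The second part stands and narrows the point. The first does not remove it, because the text gives a volume and does not say that a partial dose counts.

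2. **The event is not lost.** Recording and 24-hour reporting carry no volume threshold, and the secondary outcomes section says unexpected symptoms or signs during treatment are recorded and analysed. Listings outside the safety set may be in a fuller document. This stands: what is lost is the event's place in the safety-set rates. A reader might infer that the adverse event reporting section and the safety set contradict each other. They do not: "any adverse medical event that occurred at any dose at any time throughout the whole trial" settles which events are reportable, not who is analysed.

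3. **The requirement for safety evaluation data is not a second defect of the same kind.** A reader might infer that it too removes patients who react and leave early. But a recorded reaction is arguably safety data in itself, and Data collection and management plans to seek outcome data after withdrawal. The clause mainly removes patients with no safety observation at all. Deleting it would mostly add patients without events to the denominator and lower the reported rate. It needs clarification, not removal.

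4. **The numbers are likely small.** Pilot observation is said to show good tolerability, and patients with an allergic constitution or a known allergy to an ingredient are excluded. This stands, and zero affected patients is plausible.

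**Conclusion.** The point holds in a narrow form. The 20 mL threshold leaves an exposed patient who stops partway through the first dose outside every defined analysis set, and an adverse event in that patient is missing from the safety-set rates. The exclusion can be caused by the drug. Where the excluded patient had a reaction, the error goes one way: it hides immediate intolerance.

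The size cannot be taken from the documents. It is nil if nobody stops before completing a dose. Under the assumption of one or two such patients among 180, a rate of 0.6% or 1.1% for immediate reactions is shown as zero, and the upper limit falls from 3.1% or 4.0% to about 2%. These figures do not support saying that a safety signal will disappear from the trial, since the events stay in the adverse event records and, if serious, in the expedited reports. The point deserves correction because the wording is fixed in the document and changing it is nearly free, not because a large bias has been shown.

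**What to change.** Replace the safety set definition with wording such as: all randomized participants who took any amount of trial medication; a recorded adverse event counts as safety evaluation data. For laboratory tables, report the number of participants with a post-baseline value for each test.

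The change is one sentence, made before unblinding. It needs no new data and no change to dosing or sample size. If it is judged a significant change to the data analyses, it goes through the ethics committee step described under Ethical considerations and dissemination. The downside is that the reported adverse event rate may be slightly less favourable.

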## Background

Acute bronchitis (AB) is a common clinical condition characterized by acute inflammation of the trachea and lower airways. About 95% of uncomplicated AB patients are caused by viral infections, and bacterial infections are not common [1, 2]. Approximately 5% of adults have an episode of AB per year, accounting for more than 10 million medical visits each year [3]. Patients predominantly present with cough with or without sputum production without evidence of pneumonia. Cough usually lasts no more than 3 weeks and is the major reason for both outpatients consultations and emergency departments attendances.

Although AB is considered to be self-limiting in most cases, symptomatic treatment is primarily required, particularly improving cough. Antibiotic agents have been widely but unnecessarily used worldwide. However, antibiotics use can only provide a modest reduction of cough duration by 0.46 days, and unnecessary antibiotics use may be associated with high antibiotic cost, increased antibiotic resistance, and potential side effects [4]. Therefore, antibiotics are not recommended for routine use in uncomplicated AB patients [5, 6]. Similarly, antiviral therapy, inhaled corticosteroids, inhaled beta agonists, inhaled anticholinergics, oral corticosteroids, antitussives, oral non-steroidal anti-inflammatory drugs, or alternative therapies are also not recommended for routine use in clinical practice for effectiveness and safety concerns [3, 7].

Chinese herbal medicine, an important part of complementary and alternative medicine, has been widely used in the management of AB [8]. However, evidence-based data is still lacking. Tanreqing oral liquid is a new sixth category oral drug of traditional Chinese herbal medicine jointly developed by Henan Xinyi Pharmaceutical Co., Ltd., and Beijing Jifatang Institute of Chinese Medicine. It is primarily composed of Huangqin (Radix Scutellariae Baicalensis), Xiongdanfen (Fel Selenarcti), Shanyangjiao (Cornu Naemorhedi), Jinyinhua (Flos Lonicerae), and Lianqiao (Forsythiae Fructus) and has the effects of clearing heat, detoxifying, resolving phlegm, and suppressing cough and has anti-infection and anti-inflammatory potential [9, 10]. Tanreqing oral liquid is an extension product of Tanreqing injection, which has been widely used in inpatients and emergency patients with bronchitis or pulmonary infections in China [11, 12].

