**Inclusion criteria**	
1. Diagnosis of acute bronchitis	
2. Phlegm-heat obstructing lungs syndrome in traditional Chinese medicine Zheng	
3. Total cough symptom score ≥ 4 points	
4. Expectoration in traditional Chinese medicine symptom score ≥ 6 points	
5. Bronchitis severity score ≥ 6 points	
6. Disease course within 72 h	
7. Aged 18 to 65 years old	
8. Voluntarily provide written and informed consent	

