#### Secondary outcomes

The following are the secondary outcomes:Change of bronchitis severity scores from baseline to post-treatment: Bronchitis severity score (BSS) is an observer-rated tool for assessing the severity of five major symptoms of AB including cough, sputum production, rales/rhonchi (auscultation), chest pain during coughing, and dyspnea, each rating from 0 to 4 points. The BSS is the sum of the five ratings ranging from 0 to 20 points [17].Cough relief rate: Cough relief will be defined as both daytime and nighttime CSS decreasing to 1 or less, or decreasing by 1 and lasting for two consecutive days. Cough relief rate will be the proportion of patients who achieve cough relief after treatment.Time to cough resolution: length of time at baseline to cough resolution: For example, the daytime and nighttime CSS on the patient’s diary cards on the 5th and 6th days are all 0 points, then the cough resolution time is recorded as “5 days.”Time to cough relief: Length of time at baseline to cough relief.Resolution rate of single TCM symptom.Combination medication use: Combination medication here will only include antibiotics, expectorants, and antitussives.Change of TCM syndrome score from baseline to post-treatment: Each TCM symptom will be graded (see Additional file 1). TCM syndrome score will be the sum of the main symptom score and all minor symptoms scores.Adverse events: Besides routine blood, urine, and stool tests and hepatic and renal functions, any unexpected symptom or sign during the treatment period will be recorded and analyzed.

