### Data collection and management

Research medical records will be the original documents in this trial, which will be properly kept by each study center. Trained researchers will collect baseline demographic parameters, outcome data, and other trial data at each visit. All participants will be instructed to grade their cough and TCM symptoms and record medication use and any unexpected condition on the daily diary card.

Plans to promote participant retention will be as follows: (1) instructing participants to fully understand the importance of study involvement and acknowledging their participations (2); recording contact details of participants to keep them in touch, including mobile phone, QQ, WeChat, and email (3); calling to remind participants one day before a scheduled visit (4); trying to re-contact or re-schedule at their convenient time in case of a missed visit (5); trying to collect outcome data when a participant withdraws from the study; and (6) providing a compensation of ¥600 after completing follow-up.

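### Last observation carried forward holds dropouts at an earlier, higher bronchitis severity or TCM syndrome score in a self-limiting disease, so unequal dropout between arms biases these two secondary comparisons in either direction

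*Protocol article*

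**What the plan says.** The protocol article, Statistical analysis, fixes one rule for all missing efficacy values: "Missing efficacy data will be imputed using the last observation carried forward method". It names no other method. Quantitative secondary outcomes are to be compared by t test or nonparametric test at a one-sided 0.025 level, in the full analysis set and the per-protocol set.

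Two secondary outcomes are quantitative scores measured as a change. One is the observer-rated BSS: "The BSS is the sum of the five ratings ranging from 0 to 20 points". The other is listed as "Change of TCM syndrome score from baseline to post-treatment". Entry requires "Bronchitis severity score ≥ 6 points".

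On the natural course, the Background says: "Although AB is considered to be self-limiting in most cases".

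The section on withdrawal and termination lists a rise in temperature to 39 °C or more, marked worsening after three treatment days, serious adverse events or allergic reactions, and use of forbidden medication. Among patients' own reasons for leaving it gives poor efficacy and intolerable adverse reactions. Sample size calculation expects 20% dropout after randomization, not split by arm, with 180 patients on Tanreqing and 90 on placebo.

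Data collection and management sets up a daily diary card: "All participants will be instructed to grade their cough and TCM symptoms". It also says that staff will try to obtain outcome data from patients who withdraw.

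**The concern.** LOCF assumes that a patient who leaves stays at the last recorded score. For a disease that mostly clears by itself, that conflicts with the protocol's own description. A patient last scored on day 3 is entered at the end of treatment with a day-3 score, although further improvement would be expected in either arm.

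This understates improvement in both arms, and the comparison escapes only if the two errors are equal. Several listed withdrawal reasons depend on how well the treatment works or is tolerated, so an active drug and a placebo may well lose different numbers of patients, or lose them at different times. A score difference could then arise from dropout alone, or a real one could be hidden. These are formal efficacy comparisons with a significance rule, in a trial planned around the regulatory requirements for a new drug.

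**Working it through.** **Inputs from the protocol.** Arms 180 and 90; overall dropout 20%; treatment for 7 days; one-sided 0.025; t test; BSS range 0 to 20 with at least 6 at entry.

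**Assumed, because the documents do not give them.** The mean score falls linearly from 9 to 3 over 7 days; dropouts are last scored on day 3; within-group SD is 2.5 to 3.0; dropout is split by arm as shown below.

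The plan has no figure of its own for the scores. Its sample size of 63 on placebo concerns the primary outcome. It reproduces as (1.960 + 0.842)² / 0.2² × (0.16/2 + 0.24) = 62.8, rounded up, and this point does not affect it.

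**1. Bias with no drug effect.** Fall still to come at day 3 = 6 × 4/7 = 3.43 points. Bias = (placebo dropout − drug dropout) × 3.43.

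- 15% drug, 30% placebo (overall (2 × 15 + 30)/3 = 20%): 0.15 × 3.43 = 0.51 points in favour of the drug.
- 16.7% and 26.7%: 0.10 × 3.43 = 0.34 points in favour.
- 20% and 20%: 0.
- 25% and 10% (overall 20%): 0.51 points against the drug.

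**2. False-positive rate.** Mixing completers with dropouts held 3.43 points higher adds d(1 − d) × 3.43² to an arm's variance, where d is its dropout fraction. For 15%/30% at SD 2.5:

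- Arm variances: 6.25 + 0.1275 × 11.76 = 7.75, and 6.25 + 0.21 × 11.76 = 8.72.
- Pooled SE: √[(2 × 7.75 + 8.72)/3 × (1/180 + 1/90)] = 0.367. Significance threshold: 1.96 × 0.367 = 0.719.
- Actual SE if dropout numbers vary at random: √(7.75/180 + 8.72/90) = 0.374. P(Z > (0.719 − 0.514)/0.374) = 29%.
- If dropout numbers are fixed, the actual SE is 2.5 × √(1/180 + 1/90) = 0.323, and the rate is 26%.

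The same steps for the other cases give:

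| Dropout drug / placebo | Bias (points) | SD 2.5, random / fixed numbers | SD 3.0, random / fixed numbers |
|---|---|---|---|
| 15% / 30% | +0.51 | 29% / 26% | 23% / 21% |
| 16.7% / 26.7% | +0.34 | 16% / 12% | 13% / 10% |
| 20% / 20% | 0 | 2.5% / 1.3% | 2.5% / 1.6% |
| 25% / 10% | −0.51 | below 0.1% | below 0.1% |

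Simulated t tests (20,000 runs per cell, random dropout numbers) gave 29% and 23% for the first row, 15% and 12% for the second, 2.5% and 2.3% for the third, and below 0.1% for the last. A separate simulation with fixed numbers gave about 26% and 20% for the first row.

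**3. Equal dropout with a real effect.** Let day-7 means be 2 (drug) and 4 (placebo), both from 9, with 20% dropout in each arm. LOCF difference = 0.8 × 2 + 0.2 × 2 × (day of last score)/7. This gives 1.60, 1.66, 1.77 and 1.89 for a last score on day 0, 1, 3 and 5, against a true 2.0.

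**4. Hiding a real effect.** Under a second set of assumptions (mean fall 7 on drug and 6 on placebo, a true benefit of 1 point; dropouts half recovered; SD of change 2.5), simulated power was 87% with no dropout and 69% with 20% in each arm. It was 35% with 23.3% drug / 13.3% placebo and 10% with 26.7% / 6.7%. The expected LOCF difference in the third case is 7 × (1 − 0.5 × 0.233) − 6 × (1 − 0.5 × 0.133) = 0.58 points.

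**The case against.** **The false-benefit case is one-sided.** A drug that does nothing should not halve efficacy-related dropout, and a drug that causes reactions would lose more patients itself, which biases against it. This stands. The documents give no split by arm, so the false-benefit figure is one of two directions and must be read with its reverse.

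**Mitigation is planned.** Staff will reschedule missed visits and try to obtain outcomes after withdrawal, so 20% dropout need not mean 20% of scores held at day 3. This also stands. It shrinks the bias but does not remove it, because it is an effort and not a guarantee.

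**Baseline carry-forward is limited.** A reader might infer that many BSS changes will be set to zero. The full analysis set requires outcome data after treatment, so this could arise only for a patient with other post-treatment data, such as diary entries, but no later BSS. The BSS visit times are in a figure not shown.

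**Standard errors.** A reader might infer that LOCF makes them invalid here. The check does not show that: each patient contributes one value, and with equal dropout and no effect the simulated t test stays close to 2.5%. The fault shown is bias in the mean difference.

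**The analysis plan may add sensitivity analyses.** It may, but the protocol already states LOCF as the rule. The objection is to a stated method and not to missing detail. The per-protocol analysis does not repair the imputation.

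**Conclusion.** The point holds for the two secondary scores. LOCF conflicts with the expected course of the disease and biases the comparison whenever dropout or its timing differs between arms. The listed withdrawal reasons make that plausible.

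The mechanism and its direction follow from scores falling over time; the size rests on the assumed trajectory, SD, dropout day and split. On those assumptions a 15-point gap with more placebo dropout gives 0.51 points and roughly 20% to 29% false positives, and a 10-point gap gives roughly 10% to 16%. The same gaps reversed bias against the drug and can hide a benefit.

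A reader might go further and conclude that neither score result could be interpreted at 20% dropout. The documents do not support that. With equal dropout and timing, a null comparison is unbiased and a true 2.0 becomes about 1.6 to 1.9, a conservative dilution. Nor does this point bear on the primary cough resolution rate. It should be corrected, but it does not threaten the trial's main conclusion.

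**What to change.** For these two outcomes, make LOCF a sensitivity analysis and name a different main method.

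- **TCM syndrome score:** a mixed model for repeated measures on the daily diary grades, with baseline score, treatment, day, treatment-by-day and centre, reporting the day-7 difference. This applies where the score can be built from the diary; the article does not say that it can, so the plan should confirm it.
- **BSS:** multiple imputation of a missing end-of-treatment rating from baseline BSS, treatment and the diary scores.
- **Sensitivity:** both methods assume data missing at random. That is doubtful for patients withdrawn for worsening or fever, who would be given the recovery of similar patients who stayed. Add an analysis that does not assume recovery for them, for example reference-based or delta-adjusted imputation.
- **Reporting:** show dropout by arm, day and reason, so that readers can judge the bias.

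The cost is revised analysis wording and standard SAS code on data already being collected, with no new visits or patients. The protocol already provides for ethics approval of significant changes to data analyses. The change should be fixed before unblinding.

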### Outcome measures

#### Primary outcome

Cough resolution rate: proportion of patients whose cough is completely resolved after treatment.

The overall frequency, severity, and impact of cough will be evaluated using a patient self-rated cough symptom score (CSS) scale. CSS scale will be graded twice daily at two intervals: daytime (from 8:00 am to 8:00 pm) and nighttime (from 8:00 pm to 8:00 am), each scored from 0 to 3 points [16]. Cough resolution will be defined as both daytime and nighttime CSS scale reduced to 0 without relapse for two consecutive days.

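### The named primary test of cough resolution ignores the baseline cough symptom score; prespecifying an adjusted risk difference would be a cheap, optional gain in precision

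*Protocol article*

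**What the plan says.** The Statistical analysis section of the Protocol article fixes the primary test: "The primary outcome of cough resolution rate will be analyzed using the chi-squared" or Fisher's exact test. It then adds a second analysis of the same outcome, "Furthermore, logistic regression will be conducted to provide a risk ratio", and lists no covariates for that model. It also refers to a separate document: "Statistical analysis will be performed using SAS 9.4 according to the statistical analysis plan".

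Under Primary outcome, cough is "evaluated using a patient self-rated cough symptom score (CSS) scale". Scores are given for the day and for the night, the latter defined as "nighttime (from 8:00 pm to 8:00 am), each scored from 0 to 3 points", with the same range by day. Resolution requires both scores to be 0 for two consecutive days.

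Table 2 makes the same scale an entry condition: "Total cough symptom score ≥ 4 points". Every randomized patient therefore has a baseline CSS.

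The Sample size calculation section works with a crude difference in proportions: 0.80 versus 0.40, a margin of 0.2, one-sided 0.025, 80% power and 2:1 allocation. This gives 126/63, which is raised to 150/75 for regulatory reasons and to 180/90 for dropout.

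**The concern.** The endpoint is a fall of the CSS to 0 within a seven-day treatment course. A patient who starts at 3 by day and 3 by night has further to fall than one who starts at 2 and 2, so baseline CSS is a plausible predictor of resolution. The named primary test makes no use of it. The logistic regression is described only as a way to obtain a risk ratio, and even if it carried covariates the named test would remain unadjusted.

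What is at stake is the width of the confidence interval for the difference in resolution rates and, depending on the null tested, some power. The data needed for the adjustment are already collected.

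**Working it through.** **Inputs from the document.** Rates 0.80 and 0.40; margin 0.2; one-sided alpha 0.025; beta 0.2; ratio 2:1; planned numbers before dropout 150/75. Day and night scores each run from 0 to 3. Taking the total as their sum, it runs from 0 to 6, and the entry rule leaves only 4, 5 and 6.

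**Assumptions, because the document is silent.** The distribution of baseline CSS over 4/5/6, and the odds ratio (OR) per point. An OR of 2 to 3 against resolution is the same as an OR of 0.5 to 0.33 for resolution.

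**1. The plan's own figure.** n(placebo) = (1.96 + 0.8416)² / (0.8 - 0.4 - 0.2)² × [0.8×0.2/2 + 0.4×0.6] = 7.849 / 0.04 × 0.32 = 62.8. This rounds up to 63, and to 126 at 2:1, so the stated 126/63 reproduces.

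**2. Unadjusted precision at 150/75.** Var = 0.16/150 + 0.24/75 = 0.004267, SE = 0.0653, 95% half-width 0.128. Power against the margin = Phi(0.2/0.0653 - 1.96) = Phi(1.10) = 86.5%. Against a zero null at 0.80 versus 0.40 it exceeds 99.9%.

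**3. Adjusted variance.** Var(adj) = Σw·qT(1-qT)/150 + Σw·qC(1-qC)/75 + Σw(qT - qC - 0.4)²/225. Here w is the share of patients at each CSS value, and qT and qC are the resolution rates at that value.

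Example with shares 50/30/20% and OR 0.5 for resolution:
- qC = 0.51, 0.34, 0.21 and qT = 0.88, 0.78, 0.64.
- The weighted within-level variances are 0.225 (placebo) and 0.150 (Tanreqing).
- Var(adj) is about 0.00401, or 5.9% below 0.004267 with these rounded rates. Unrounded, the reduction is 5.7%.
- Power = Phi(0.2/0.0634 - 1.96) = 88.4%.

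**4. Range at 0.80 versus 0.40, 150/75** (shares 50/30/20% and equal thirds):

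| OR per point for resolution | Variance reduction | Power against 0.2 margin |
|---|---|---|
| 1.0 | 0% | 86.5% |
| 0.8 | 0.6-0.7% | 86.7% |
| 0.67 | 2.0-2.2% | 87.1-87.2% |
| 0.5 | 5.7-6.3% | 88.4-88.5% |
| 0.33 | 12.8-14.2% | 90.7-91.1% |

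**5. Cross-check by correlation.** Variance falls by rho². With shares 40/35/25%, rho is 0.22-0.25 at an OR of 2 per point and 0.34-0.38 at 3. Rho² then runs from 0.22² = 0.048 to 0.38² = 0.144, a fall of about 5-14%. Power = Phi(0.2/(0.0653×√(1 - rho²)) - 1.96), which is 88.1% to 91.1%.

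**6. A smaller true effect.** At 0.60 versus 0.40 with a zero null, power at 150/75 is 82.3% unadjusted. It becomes 84.7-85.0% at OR 0.5 and 87.6-88.3% at OR 0.33.

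**7. Validity of the unadjusted test.** Its simulated one-sided type I error (200,000 trials per scenario) was 0.0240, 0.0242 and 0.0243 at OR 1, 0.5 and 0.33, against a nominal 0.025.

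**8. Chance imbalance.** With shares 50/30/20% the SD of baseline CSS is 0.78, so the SD of the difference in means is 0.78 × √(1/75 + 1/150) = 0.11 points. At 0.80 versus 0.40, a 1.96-SD imbalance moves the risk difference by about 0.01 (OR 0.8) to 0.04 (OR 0.33). At 0.60 versus 0.40 it moves it by up to about 0.05. The unadjusted half-widths are 0.128 and 0.136.

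**The case against.** The strongest case against is that nothing here is wrong. An unadjusted comparison of two proportions in a randomized, double-blind trial is valid, and it matches a sample size built on a crude difference. That stands, and it is why the point is optional.

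The second objection is that the unseen statistical analysis plan may list covariates for the logistic regression. That also stands: a reader might infer that no adjusted analysis is planned, and the article does not show this. It shows only that the test it names for the primary outcome is unadjusted. The point therefore challenges a stated choice, not a silence.

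Three stronger readings are tempting and should not be made:

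- **That chance imbalance in baseline CSS threatens the primary result.** Randomization makes such imbalance part of the sampling variation that the unadjusted interval already covers (steps 7 and 8). Only conditional precision is affected, which is the same loss of precision and not a second problem.
- **That the gain is 8 to 10 power points.** This needs rho 0.5: 80.1% to 90.0% at 126/63, or 85.1% to 93.4% at 144/72 (270 less 20%). With shares 40/35/25%, rho 0.5 means an OR of about 5 per point on placebo (resolution about 68%, 30% and 8% at CSS 4, 5 and 6) and more than 6 on Tanreqing. Nothing in the document supports that for a score confined to three values. Also, 126/63 is an intermediate figure, not the planned size.
- **That the trial is underpowered without adjustment.** Unadjusted power at 150/75 is 86.5% against the margin, above the 80% target. An ordinary chi-squared test has a zero-difference null, and there power at the design rates is above 99.9% either way.

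**Conclusion.** The point holds as an optional efficiency improvement. The primary test leaves out a baseline measure of its own endpoint, at some cost in precision if that measure is prognostic. On an assumed OR of 2 to 3 per CSS point and the assumed score distributions, the variance falls by about 5-14%, and power against the 0.2 margin gains about 2 to 5 points at 150/75. If CSS is weakly prognostic (OR for resolution 0.8 per point), the variance gain is under 1%. Against a zero null at 0.80 versus 0.40, the benefit is a narrower interval and nothing more. The unadjusted result would be neither biased nor invalid.

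**What to change.** Prespecify the primary estimate as the difference in cough resolution rates standardised over all FAS patients, from a logistic model with treatment and baseline total CSS, with a robust or bootstrap 95% confidence interval. This keeps the risk-difference scale on which the trial was sized, and the two-sided 95% interval corresponds to the one-sided 0.025 level. Keep the chi-squared or Fisher's exact test as supportive. The same adjustment can be applied to the cough relief rate.

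The cost is one model statement and a standardisation step in SAS 9.4, with no new patients, visits or data. The only analytic downside is a slightly more complex primary analysis. Because the article names the primary test, the change may need the protocol modification and ethics approval that it requires for significant changes to data analyses (Ethical considerations and dissemination). It should be settled before unblinding.
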